**2.4.5.5 Analyses of vital sign variables**

The summary statistics (including number, mean, median, standard deviation, minimum and maximum) of all vital signs variables (SBP, DBP, HR and changes from baseline) will be calculated for each study assessment (baseline, each post-baseline time point, last on-study) by intervention arm. For these parameters mean changes from baseline with the corresponding standard error will be plotted over time (at same time points) in intervention arm.

The total number and percentage of participants presenting at least one post-baseline abnormality in SBP, DBP or HR, as per the threshold defined in the protocol (list provided in Appendix B) will be presented by intervention arm, irrespective of the baseline level and according to the following baseline categories:

- Normal/missing
- Abnormality criteria as defined in the protocol

**2.4.6 Analyses of pharmacokinetic and pharmacodynamic variables**

Not applicable

## 2.4.7 Analyses of quality of life variables

The analysis of data from EQ-5D -5L instrument will be performed on all randomized participants with a baseline SPPB score  $<8$  assigned by randomization, and on all randomized participants with a baseline SPPB score  $\geq 8$  assigned by randomization separately.

Baseline is defined as the randomization visit V1 (T0) evaluation. Analysis window will be used to assign time points (see Section 2.5.4).

The same MMRM model, as described in section 2.4.4.2 will be used to analyze the change from baseline in EQ-5D-5L index utility score, as well as the change from baseline in EQ-5D-5L VAS.

In addition, results per time point for all planned time points visits (value at visits using analysis windows, and changes from baseline) will be summarized and plotted using LS mean and SE for each intervention group obtained from the same MMRM models with raw values and changes from baseline as response variable in the model as appropriate. For weight, similar summary will be provided, but the percent change from baseline will be presented instead.

## 2.5 DATA HANDLING CONVENTIONS

### 2.5.1 General conventions

The following formulas will be used for computation of parameters.

#### *Date of visit*

The date of the anthropometry exam is considered as the date of visit. In case the date of anthropometry is missing, the following order of available dates is considered:

- Date of exam from the “400-meter walk test” e-CRF form
- Date of exam from the “ADL Proxy” e-CRF form
- Date of exam from the “Assistive Device Questionnaire” e-CRF form
- Date of exam from the “PAT-D” e-CRF form
- Date of exam from the “Outcome events” e-CRF form

#### *Medical history*

“Cardiovascular medical history” is defined using pre-listed items under the “Cardiovascular” subsection of the e-CRF page “Medical History”: if any of the pre-listed questions below is answered “Yes” then the participant is considered having a cardiovascular medical history:

- Has a doctor ever told you that you have high blood pressure or hypertension?

- Are you currently taking any medicine for your high blood pressure?
- Has a doctor ever told you that you had a heart attack, or coronary, or myocardial infarction and you had to be hospitalized overnight?
- Has a doctor ever told you that you had heart failure or congestive heart failure?
- Has a doctor ever told you that you had angina or chest pain due to blockage in the arteries of your heart?
- Have you had coronary artery bypass surgery ?
- Have you ever had a stent and/or angioplasty of the coronary arteries, which is a dilation of the arteries of the heart with a balloon?
- Have you ever had a carotid endarterectomy, which is surgery on the arteries in your neck to improve blood flow to your brain?
- Do you have a pacemaker?

“Diabetes medical history” is defined using pre-listed items under the “Diabetes” subsection of the e-CRF page “Medical History”: if any of the pre-listed questions below is answered “Yes” then the participant is considered having a diabetes medical history:

- Has a doctor ever told you that you had diabetes, sugar in your urine, or high blood sugar?
- Are you now using medication that you swallow to treat or control your diabetes?
- Are you now using insulin injections?

“Neurologic medical history” is defined using pre-listed items under the “Neurologic” subsection of the e-CRF page “Medical History”: if any of the pre-listed questions below is answered “Yes” then the participant is considered having a neurologic medical history:

- Has a doctor ever told you that you had a transient ischemic attack (TIA) or mini-stroke?
- Has a doctor ever told you that you had a stroke or brain hemorrhage and had to be hospitalized?

“Musculoskeletal medical history” is defined using pre-listed items under the “Musculoskeletal” subsection of the e-CRF page “Medical History”: if any of the pre-listed questions below is answered “Yes” then the participant is considered having a musculoskeletal medical history:

- Has a doctor ever told you that you had a broken or fractured hip and had to be hospitalized?
- Since the age of 50, have you ever been told by a doctor, nurse, therapist, or medical assistant that you had broken or fractured any other bones?

“Arthritis medical history” is defined using pre-listed items under the “Arthritis” subsection of the e-CRF page “Medical History”: if any of the pre-listed questions below is answered “Yes” then the participant is considered having an arthritis medical history:

- During the last 6 months, have you seen a doctor specifically for arthritis or rheumatism?
- Did you have pain and/or stiffness in any of the following joints? (Hands/Fingers, Shoulders, Knees, Hips, Back/spine, Foot)

### ***Disease characteristics at baseline***

The 400-m walk speed in m/s is the ratio of 400 divided by the time to walk 400 meters in seconds.

### ***Rate of adverse events per patient-year***

Computed as [sum of number of events for all analysis population] / [sum of patient-year of study participation for all analysis population], with patient-year of study participation calculated per participant as number of days from date of randomization visit V1-T0 (or date of randomization if V1 is missing) to end date of study participation as reported by investigators in the End of study e-CRF page divided by 365.25.

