#### **5.1.4. Temporary suspension of the screening procedures**

In many cases, participants may have conditions that would preclude participation in the study that could resolve. Therefore, we also define a set of criteria temporary suspending the procedures for validation of the subject's eligibility. Participants presenting such conditions may be re-contacted later during the recruitment period for completing the evaluation on a second time (in order to maximise the recruitment activities and avoiding losing the inclusion of potential participants due to temporary conditions).

This approach has already been adopted in previous RCTs, such as the LIFE and the DO-HEALTH (<http://do-health.eu>) studies.

*Subjects excluded for one of the temporary medical conditions listed below can be rescreened after a period that is considered clinically relevant by the local study physician. The participant will maintain the same informed consent form and will not change his/her participant ID. Nevertheless, all the eligibility criteria (not only those having temporarily suspended the eligibility validation) will be checked. This approach will maximize the efficacy of the recruitment strategies and (in parallel) avoiding double versions of signed informed consent forms and participant's ID for the same individual.*

- h. Uncontrolled hypertension (systolic blood pressure >200 mmHg, or diastolic blood pressure >110 mmHg)
- i. Uncontrolled diabetes with recent weight loss, diabetic coma, or frequent hypoglycaemia
- j. Hip fracture, hip or knee replacement, or spinal surgery in the past 6 months
- k. Serious cardiac conduction disorder (e.g., third-degree heart block), uncontrolled arrhythmia, new Q waves within the past 6 months or ST-segment depression (>3 mm) on the ECG
- l. Myocardial infarction, major heart surgery (i.e., valve replacement or coronary bypass graft), stroke, deep vein thrombosis, or pulmonary embolism in the past 6 months
- m. Use of growth hormone, oestrogens, progesterone, or testosterone supplementation in the past 3 months

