## **7. Measures and procedures**

### **7.1. Informed Consent**

Informed consent must be obtained before participants are screened. Verbal consent will be acquired prior to the administration of the telephone screen.

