#### **7.4.3. Randomisation**

##### **7.4.3.1. Final Eligibility Assessment**

Data related to eligibility and key measures will be entered prior to randomisation. A computerized check will be performed to confirm that all required elements are entered and are within range prior to randomization.

Eligibility is dependent on screening data being collected within a set timeframe: all screening data have to be collected within 60 days (i.e., the time between the date of the telephone screening interview and the date of randomisation cannot exceed 60 days), including key clinical and performance measures (400-metre walk; weight). The computerised eligibility check does not permit randomisation if dates of data collection are

outside of these ranges. If a screenee is ineligible, staff will determine whether this may be due to a temporary condition (e.g., blood pressure out of range or too young of age) and discuss this with the participant. Re-screening can be conducted at a later date in such situations.

The allowable time from the date of randomisation to the date of the first individual intervention will be two months. Randomisations will be timed at the clinic sites to allow these deadlines to be met.

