#### *Adverse event observation period:*

AEs are classified into three distinct categories:

- Pre-emergent adverse events are adverse events that occurred from the signed informed consent date up to the randomization visit V1-T0 or date of randomization if V1 is missing (included)
- Emergent adverse events (EAE) are adverse events that occurred from the randomization visit V1-T0 or date of randomization if V1 is missing (excluded) up to the end date of study participation (included)
- Post-emergent adverse events are adverse events that occurred after the end date of study participation

All adverse events are coded to a lower-level term (LLT), preferred term (PT), high-level term (HLT), high-level group term (HLGT), and associated primary system organ class (SOC) using the version of Medical Dictionary for Regulatory Activities (MedDRA) currently in effect at Sanofi at the time of database lock.

In SPRINTT study, SAEs criteria include the following events:

- Death,
- In-patient hospitalization
- Life threatening illness or accident,

- Permanent disability or incapacity
- Other serious illness that might have results in an SAE without aggressive medical intervention

AEs that occurred while under the supervision or guidance of study related personnel include:

- AE that meets criteria for SAE
- Event requiring active intervention by research staff to reduce potential harm
- Chest pain for more than two minutes after stopping exercise
- Dyspnea for more than two minutes after stopping exercise
- Vital signs out of range (systolic BP  $\geq 250$  mmHg or diastolic  $\geq 115$  mmHg, HR  $>120$  beats/minute or  $< 45$  beats/minute) for more than two minutes after stopping exercise
- A fall during study recommended activity
- A symptom or illness that developed and required medical management or attention

Adverse events of special interest include:

- Emergency room or urgent care visit
- Fracture
- Outpatient surgery
- Abnormal laboratory or diagnostic test result requiring immediate medical attention
- Restricted activity due to health problem potentially related to the study activity that led an inability to leave home for at least one week

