### ***Analysis of all emergent adverse events***

The following emergent adverse event summaries will be generated:

- Overview of emergent adverse events, summarizing number (%) of participants with at least one event and number and rate per patient-year for:
  - Pre-emergent adverse event
  - Emergent adverse event
  - Serious emergent adverse event
    - Death,
    - In-patient hospitalization
    - Life threatening illness or accident,
    - Permanent disability or incapacity
    - Other serious illness that might have results in an SAE without aggressive medical intervention
  - Emergent unexpected event that may be related to study procedures
  - Emergent adverse event that occurred while under the supervision or guidance of study related personnel
    - AE that meets criteria for SAE
    - Event requiring active intervention by research staff to reduce potential harm
    - Chest pain for more than two minutes after stopping exercise
    - Dyspnea for more than two minutes after stopping exercise
    - Vital signs out of range (systolic BP  $\geq 250$  mmHg or diastolic  $\geq 115$  mmHg, HR  $>120$  beats/minute or  $< 45$  beats/minute) for more than two minutes after stopping exercise
    - A fall during study recommended activity
    - A symptom or illness that developed and required medical management or attention

- Emergent adverse event of special interest
  - Emergency room or urgent care visit
  - Fracture
  - Outpatient surgery
  - Abnormal laboratory or diagnostic test result requiring immediate medical attention
  - Restricted activity due to health problem potentially related to the study activity that led an inability to leave home for at least one week
- All emergent adverse events by primary SOC, HLGT, HLT, and PT, showing number (%) of participants with at least 1 emergent adverse event and number of events and rate per patient-year sorted by the SOC internationally agreed order. The other levels (HLGT, HLT, PT) will be presented in alphabetical order
- All emergent adverse events by primary SOC and PT, showing the number (%) of participants with at least 1 emergent adverse event and number of events and rate per patient-year, sorted by the internationally agreed SOC order and by decreasing incidence of PTs within each SOC in the MCI group.

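### The pre-emergent adverse event row is given a rate per patient-year whose denominator starts at randomisation, when the period for those events ends

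*Combined protocol and SAP*

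**What the plan says.** Three parts of the SAP fix the calculation.

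- **Which events count.** SAP 2.1.4.1, under the adverse event observation period: "Pre-emergent adverse events are adverse events that occurred from the signed informed consent date up to the randomization visit". The day of that visit is included. Emergent events start after it and run to the end of study participation.
- **Which statistic is planned.** SAP 2.4.5.1, under the analysis of all emergent adverse events: "Overview of emergent adverse events, summarizing number (%) of participants with at least one event and number and rate per patient-year for" a list of categories. Pre-emergent events come first and emergent events second. Nothing exempts the first row from the rate.
- **How the rate is computed.** SAP 2.5.1 divides the number of events by summed patient-years, "with patient-year of study participation calculated per participant as number of days from date of randomization visit V1-T0" (or from the date of randomisation if that visit is missing) "to end date of study participation as reported by investigators in the End of study e-CRF page divided by 365.25". This is the only patient-year definition in the SAP, and it has no separate rule for pre-emergent events.

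**The concern.** A rate per patient-year means something only if the events counted could have occurred during the time counted. Here they could not, apart from the randomisation day itself. A programmer who follows the text will divide screening-period events by follow-up time. The result depends on the wrong quantity: extending follow-up lowers it, although nothing about screening has changed.

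What is at stake is the reading of one table. The pre-emergent and emergent rates stand in adjacent rows, in the same units, for participants aged 70 or older, of whom one arm begins an exercise programme. If the true event rate were the same before and after randomisation, the table would still show a much higher rate afterwards in both arms.

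**Working it through.** The plan states no adverse event rate, no person-time before randomisation and no expected number of screening events, so it has no figure to reproduce. The check is how far the defined denominator differs from the matching one.

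**Formula.** Let S be the mean number of days from signed consent to the randomisation visit, and F the mean number of years from that visit to the end of participation. The matching denominator is S/365.25 years per participant; the defined one is F. Therefore:

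understatement factor = F × 365.25 / S

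With a constant true event rate, the same factor is the apparent ratio of the emergent rate to the pre-emergent rate.

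**Inputs.**

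- *F.* SAP 1.4 gives a minimum of 2 years and up to 3 years. Protocol 4.1 foresees an average of 2.7 years. The range used is 2 to 2.7.
- *Dropout.* SAP 1.3 assumes exponential dropout of 25% over 2 years, so the hazard is −ln(0.75)/2 = 0.1438 per year. Mean observed time for planned follow-up T is (1 − exp(−0.1438 T))/0.1438, which gives 1.738 years at T = 2 and 2.237 years at T = 2.7.
- *S.* Not stated. The flowchart (protocol 7.3, SAP Appendix A) marks informed consent at the first screening visit, whose window is the 30 days before T0. That is a maximum window, not a duration. Two provisions bear on longer intervals. Protocol 7.4.3.1 says "the time between the date of the telephone screening interview and the date of randomisation cannot exceed 60 days", but that clock starts at the telephone interview, which needs only verbal consent under protocol 7.1. Protocol 5.1.4 lets temporarily excluded people be rescreened later: "The participant will maintain the same informed consent form and will not change his/her participant ID". For them, signed consent can precede randomisation by more than 30 days. S is therefore varied.

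**Numbers at S = 30 days.**

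- No dropout: 2 × 365.25/30 = 24.4; 2.7 × 365.25/30 = 32.9.
- With dropout: 1.738 × 365.25/30 = 21.2; 2.237 × 365.25/30 = 27.2.

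**Results for other values of S.**

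| Consent to randomisation | No dropout, 2 to 2.7 years | With planned dropout, 2 to 2.7 years |
|---|---|---|
| 14 days | 52.2 to 70.4 | 45.3 to 58.4 |
| 30 days | 24.4 to 32.9 | 21.2 to 27.2 |
| 60 days | 12.2 to 16.4 | 10.6 to 13.6 |

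Every case in the table exceeds tenfold. At the full 3 years and 30 days the factor would be 3 × 365.25/30 = 36.5 without dropout and 29.7 with it.

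**Other rows.** Emergent events run from after the randomisation visit to the end of participation, which matches the SAP 2.5.1 denominator. The serious and special-interest rows are subsets of emergent events. Their rates are sound.

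**The case against.** The strongest objection is that this row hardly matters. SAP 2.4.5.1 puts the primary focus on emergent events, SAP 2.4.5 presents safety by intervention arm, and no comparison before and after randomisation is planned. The counts and percentages in the row remain correct. All of this stands and limits the importance of the point. It does not rescue the rate: if nobody will read it, it has no reason to be in the table.

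Three stronger readings are tempting, and the documents do not support them.

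- *The error is a fixed 24- to 33-fold.* A reader might infer this from the 30-day window and 2 to 2.7 years of follow-up. It treats the maximum window as everyone's duration, and it ignores both planned dropout and rescreening under the same consent. The 2.7 years is itself a protocol forecast. SAP 1.3 later records 6 more months of accrual and 7 more months of study duration, and gives no resulting mean.
- *The table creates a false safety signal against the programmes.* The same rule applies to both arms, so it does not by itself favour either. Misreading is possible, but only through a comparison that the SAP does not plan.
- *A corrected denominator would make the two rates comparable.* The SAP 2.4.5 rules restrict safety analyses to randomised participants. Someone who had a stroke or myocardial infarction during screening would be suspended under protocol 5.1.4, and would be missing unless later rescreened and randomised. A consent-to-randomisation rate is therefore selected towards low event counts. Some collected categories also concern study-supervised activity, to which exposure differs before and after randomisation.

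**Conclusion.** The point holds as a mismatch of definitions confined to one descriptive entry. As written, the pre-emergent rate divides events from one period by time from another, and no other SAP text corrects it. The direction is certain whenever follow-up is longer than screening. The size is conditional: about 21- to 33-fold for a mean consent-to-randomisation time of 30 days, more if shorter, and about 11- to 16-fold at 60 days, all assuming 2 to 2.7 years of follow-up with or without the planned dropout. Between-arm comparisons of emergent events and all efficacy analyses are unaffected. This is a minor correction, worth making because the text cannot be followed literally and give a meaningful number.

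**What to change.** Preferred: in the SAP 2.4.5.1 overview, drop the rate per patient-year from the pre-emergent row and keep the number and percentage of participants and the number of events. This removes one table entry and needs no new data.

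If a rate is kept, add one sentence to SAP 2.5.1 defining its denominator as days from signed consent to the randomisation visit, divided by 365.25. Add a table footnote that it covers randomised participants only and is not comparable with the emergent rate. Both dates are already needed to classify events under SAP 2.1.4.1. Neither option changes a hypothesis test.

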## **2.5.2 Data handling conventions for secondary efficacy variables**

- The usual gait speed in m/s is the ratio of 4 meters walks divided by the time for the faster for the two walks in seconds (as reported in eCRF for the Gait Speed test component of SPPB).
- Changes in mood using the Center for Epidemiological Studies-Depression scale (CES-D): The score obtained with the 11-item version of the CES-D will be transformed using the procedure recommended by Kohout (3) to make it compatible with the full 20-item instrument, i.e.:
  - For males,  $(Z \text{ score} * 7.2) + 7.1$ , where Z score is the familiar standardizing transformation
  - For females,  $(Z \text{ score} * 9.1) + 10.0$

## **2.5.3 Missing data**

For categorical variables, participants with missing data are not included in calculations of percentages unless otherwise specified. When relevant, the number of participants with missing data is presented.

***Handling of adverse events with missing or partial date/time of onset***

Missing or partial adverse event onset dates will not be imputed. By default, if the partial adverse event onset date information does not indicate that the adverse event started prior to the randomization visits or after the end date of study participation as reported by investigators in the End of study e-CRF, the adverse event will be classified as emergent. No imputation of adverse event end dates will be performed.

